## **10. DATA COLLECTION AND QUALITY ASSURANCE**

### **10.1 Data Collection Forms**

All data collection forms are paper-based or electronic (eCRF) with the exception of the prescreen survey which is always an online form. As source documents, all forms are signed or electronically verified and dated by a study staff member. Forms are identified with Personal Identification Numbers with no personal identifying information. The Study Coordinator or Research Assistant transfers all data from the forms to the database. Every 2-weeks a Research Assistant performs a quality assurance check by comparing paper-based forms to data entry in the database.

All paper data collection forms will be kept in a locked file cabinet in the Study Coordinator's office or the respective offices or laboratories of the PIs. Data will also be entered into an electronic database. The data management system has been developed by the Ohio University Office of Research and Sponsored Programs. Specifically, we will use REDCap™ and Qualtrics™, both web applications for building and managing online surveys and databases. Subjects will be identified by a unique identification number and no personal identifying information will be stored in the study database or used in any of the analyses files.

### **10.2 Data Management**

This is a single site study and as such Ohio University will serve as the Coordinating Center and is responsible for all data management.

### **10.3 Quality Assurance**

#### **10.3.1 Training**

Prior to data collection, the following will take place:

1. The Steering Committee will review and approve all protocols.
2. All study personnel will be trained in all study procedures for which they are responsible.
3. The RELIEF Study Treatment provider team will undergo training to ensure successful and consistent delivery of the interventions across team members.

#### **10.3.2 Quality Control Committee**

This is a single site study and the Steering Committee will be responsible for overseeing quality control.

#### **10.3.3 Protocol Compliance**

We will monitor protocol compliance as follows:

1. The PIs will monitor visit attendance records on a monthly basis to determine whether subjects are adhering to the study protocol as designed.

2. The Steering Committee will review the summary of visit attendance records on a monthly basis to determine any deviation from the protocol.
3. The PIs and Biostatistician will annually review all protocols for compliance.

#### Protocol compliance:

1. A checklist of potential protocol violations will be created and maintained for tracking by the Steering Committee. Each protocol violation report will include the violation, whether the participant is continued in the treatment and assessment visits, the impact on the study procedures, and next steps for participant continuation. The number and type of violations will be monitored relevant to the total number of subjects recruited. Examples of protocol violations include enrollment of an ineligible subject, randomization of an ineligible subject, failure to collect all screening tests, serious adverse events not reported in a timely fashion, breach of confidentiality, subject lost to follow-up, and visits outside of time window.
2. A tracking report will be developed as part of the database to allow the study coordinator to assess recruitment, consent, participant status, upcoming visits, and outstanding assessments. Reports will be created to monitor compliance with data entry and data errors. Data errors should be limited since fields will be set to exclude implausible entries.

#### **10.3.3 Metrics**

The PIs will monitor treatment administration records on a monthly basis to determine whether study participants are receiving appropriate treatments as prescribed.

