- Randomization & Stratification: The study statistician will use the R statistical language to block-randomize treatments stratified by sex for each of the three separate experiments. Specifically, within each experiment there will be two strata within which we will create blocks of 3 patients, where treatments are permuted. Based on the randomization table the study coordinator will assign subjects to the treatment arms. In instances where multiple experiments are actively enrolling study participants and a participant meets eligibility requirements for more than one experiment, we will then use an adaptive randomization method to allocate them to one of the experiments. This method ensures that an experiment with fewer participants enrolled will have a higher allocation ratio. Specifically, with two potential experiments, the allocation ratio for Experiment  $i$  ( $p_i$ ) will be  $p_i = 1 - n_i/N$ , where  $n_i$  is the sample size for Experiment  $i$  and  $N$  is the total sample size thus far enrolled. With three active experiments, the allocation ratio will be  $p_i = (1 - n_i/N)/2$ . Note that this allocation to an experimental measurement group occurs prior to the randomization to a treatment arm.
- Masking or Blinding: In the RELIEF Study the principal investigators, the statistician, and members of the data collection team will remain blinded to intervention assignment throughout the duration of the study. They will be given the identifying codes only at the end of the study when it is necessary to interpret the results of the study. The un-blinded study coordinator, who is responsible for scheduling testing and treatment sessions, will serve to receive the study patients and escort them to the various testing and treatments sites to minimize the interaction between patients; however, the study coordinator will not participate in the assessments.

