## **5.2 Handling of Study Interventions**

Each subject will, of necessity, be aware of group assignment. However, study personnel who collect the outcome measures will be blinded to the subject's group assignment as will the PIs and the statistician.

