### Baseline Assessments

The following baseline clinical outcomes and evaluations will be obtained from all study participants, regardless of which treatment arm they are assigned to:

- Numerical Pain Rating (NPR): This scale will quantify the study candidates rating of their low back pain symptoms (see appendix).
- Roland Morris Disability Questionnaire: This form quantifies the self-reported level of disability (see appendix).
- PROMIS Pain Measures: The NIH PROMIS system will be used to assess outcomes related to pain intensity, pain interference, pain behavior, and physical function.
- Prior & Concomitant Medication Form: This form documents the study participant's recent and current medication usage for their low back pain (see appendix).
- Change in Medication Use: This form documents any changes in medication use not related to low back pain.

The following baseline physiological outcomes will be obtained based the experimental group to which they are randomly assigned to (i.e., muscular, spinal, cortical):

- Group 1 (Muscular Effects):
  - Skeletal muscle proton transverse relaxation time (T2) of the lumbar muscles.
    - Location & Assessment Team: Data will be collected at the Ohio Musculoskeletal and Neurological Institutes Biomedical Imaging Suite located in Irvine Hall at Ohio University. Blinded members of The RELIEF Study Team (i.e., blinded students, staff, and the principal investigators) will be involved with the data collection and analysis.
    - Methods: Female participants will be screened for pregnancy using a urine pregnancy test; positive results will exclude a participant from remaining in the study. Data will be collected and analyzed as we have previously

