### 6.2.3 Blinding

In the RELIEF Study the principal investigators, statistician, and members of the data collection team will remain blinded to intervention assignment throughout the duration of the study. They will be given the identifying codes only at the end of the study when it is necessary to interpret the results of the study. To guard against un-blinding, only limited data categorized by intervention assignment will be released to the study investigators (e.g. adherence data), and these data will only be provided in aggregate. Secondly, the RELIEF Study Treatment Provider Team, who cannot be blind to the treatment assignment per se, will be blinded to the specific hypotheses of the study, and they will not be involved in any assessments or analyses. Lastly, the un-blinded study coordinator, who is responsible for scheduling testing and treatment sessions, will serve to receive the study patients and escort them to the various testing and

treatments sites to minimize the interaction between patients; however, the study coordinator will not participate in the assessments.

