### Treatment Assignment Procedures

Randomization & Stratification: The study statistician will use the R statistical language to block-randomize treatments stratified by sex for each of the three separate experiments. Specifically, within each experiment there will be two strata within which we will create variable blocks of 3 or 6 patients, where treatments are permuted. Then the study coordinator will assign subjects to the treatment arms. In instances where multiple experiments are actively enrolling study participants and a participant meets eligibility requirements for *more than one experiment*, we will then use an adaptive randomization method to allocate them to one of the experiments. This method ensures that an experiment with fewer participants enrolled will have a higher allocation ratio. Specifically, with two potential experiments, the allocation ratio for Experiment  $i$  ( $p_i$ ) will be  $p_i = 1 - n_i/N$ , where  $n_i$  is the sample size for Experiment  $i$  and  $N$  is the total sample size thus far enrolled. With three active experiments, the allocation ratio will be  $p_i = (1 - n_i/N)/2$ . Note that this process would occur prior to the randomization to a treatment arm.

- Masking or Blinding: In the RELIEF Study the principal investigators, the statistician, and members of the data collection team will remain blinded to intervention assignment throughout the duration of the study. They will be given the identifying codes only at the end of the study when it is necessary to interpret the results of the study. The un-blinded study coordinator, who is responsible for scheduling testing and treatment sessions, will serve to receive the study patients and escort them to the various testing and treatments sites to minimize the interaction between patients; however, the study coordinator will not participate in the assessments.

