### **Experiment 2. Spinal Effects**

- ☐ Instrument study participant for EMG.
- ☐ Instrument study participant for motion capture.
- ☐ Perform The RELIEF Study short latency spinal reflex protocol
- ☐ Perform The RELIEF Study standardized reaching protocol.
- ☐ Perform The RELIEF Study trunk perturbation protocol.
- ☐ If necessary repeat a trial and delete prior file.
- ☐ Save files to lab secure network hard drive and back-up to cloud.

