## Visit 3 (Intervention 2): INTERVENTION ADMINISTRATION LOG

To be completed by clinician

[figure not shown] **All fields must be completed**

|                                     |                                 |                      | L1                                        | L2                                        | L3                                        | L4                                        | L5                                        |                                           |
|-------------------------------------|---------------------------------|----------------------|-------------------------------------------|-------------------------------------------|-------------------------------------------|-------------------------------------------|-------------------------------------------|-------------------------------------------|
| Pre-Intervention Assessment  | Symmetry of Active Side Bending | SBL
cm            | Transverse Process                        | FRS-L
FRS-R
ERS-L
ERS-R
NORM  | FRS-L
FRS-R
ERS-L
ERS-R
NORM  | FRS-L
FRS-R
ERS-L
ERS-R
NORM  | FRS-L
FRS-R
ERS-L
ERS-R
NORM  | FRS-L
FRS-R
ERS-L
ERS-R
NORM  |
|                                     |                                 |                      | SBR
cm                                 | P-A Translation                           | Hypermobile
Hypomobile
Normal
NA | Hypermobile
Hypomobile
Normal
NA | Hypermobile
Hypomobile
Normal
NA | Hypermobile
Hypomobile
Normal
NA |
|                                     | Intervention             | # of Thrusts Applied | 1 2 3 4
NA                             | 1 2 3 4
NA                             | 1 2 3 4
NA                             | 1 2 3 4
NA                             | 1 2 3 4
NA                             | 1 2 3 4
NA                             |
|                                     |                                 | Audible Response     | Yes No
NA                              | Yes No
NA                              | Yes No
NA                              | Yes No
NA                              | Yes No
NA                              | Yes No
NA                              |

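### The PIs' monthly review of treatment administration records (section 10.3.3) conflicts with their blinding, although they help collect and analyse the physiological outcomes

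*Supplement*

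**What the plan says.** **Blinding.** Section 6.2.3 states that the "principal investigators, statistician, and members of the data collection team will remain blinded to intervention assignment throughout the duration of the study". Sections 3 and 9.2 say the same, and section 5.2 adds that the staff who collect outcomes "will be blinded to the subject's group assignment as will the PIs and the statistician". Codes are released only at the end. Section 6.2.3 also restricts what investigators see by arm: limited data, in aggregate only.

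**The PIs' part in outcomes.** For T2, stretch reflex, trunk muscle latencies, lumbar motion and the TMS measures, section 6.2.2 names the assessment team in the same words: "blinded students, staff, and the principal investigators) will be involved with the data collection and analysis".

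**The monitoring duty.** Section 10.3.3 (Metrics): "The PIs will monitor treatment administration records on a monthly basis to determine whether study participants are receiving appropriate treatments as prescribed".

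**The record.** The treating clinician completes an Intervention Administration Log for each participant at each treatment visit. At visit 2 it counts repetitions by lumbar level. At visits 3 to 7 the field is labelled "of Thrusts Applied", with options 1 to 4 or NA. Every log also asks whether there was an audible response.

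**The concern.** The PIs are given a duty that they cannot carry out while blinded. Participants know their group (section 5.2), and the design describes itself as single-blinded on the investigator side. The blinding of those who measure and process the mechanistic outcomes therefore matters, and section 9 says the study was designed mainly around those outcomes. Some of the measurements leave room for judgement. T2 comes from regions of interest, and motor threshold from deciding where responses appear consistently. A PI who has read the treatment logs and then tests a participant at a later visit, or processes that participant's data, is no longer a blinded assessor.

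**Working it through.** No plan figure needs to be reproduced. The check sets the passages side by side and then asks which assessments the review could reach.

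1. **Can the question in 10.3.3 be answered blind?** It asks whether individual participants receive the correct treatment, so delivered treatment must be compared with assigned treatment, one person at a time. The aggregate rule in 6.2.3 cannot supply that comparison. Nor is the duty merely about attendance: the other section numbered 10.3.3 (Protocol Compliance) already gives the PIs a separate monthly check of visit attendance.

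2. **Does the record point to the arm by itself?** Section 5.1 describes a thrust and a check for cavitation only for manipulation, with at most 2 attempts per side, so 2 × 2 = 4 in all. That matches the 1-to-4 field on the log. Sham laser involves neither a thrust nor a cavitation check, and mobilization is an isometric hold without a thrust. The log has no explicit arm field in the text. Its entries therefore identify chiefly the manipulation arm, planned at 54 of 162 participants. For the other 108, telling mobilization from sham depends on how the repetition and NA options are completed.

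3. **Is masking stated?** Section 7.2 has the coordinator prepare masked adverse event reports before the PIs see them. Section 10.3.3 (Metrics) states no masking, pooling or delegate.

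4. **Which assessments come after a review?** OA1 and OA2 are both collected at visit 2, immediately before and after the first treatment. No monthly review can have shown a treatment log for that participant by then. For OA3 and OA4, assume that visit 2 is day 1, that reviews are 28 to 31 days apart and unrelated to enrolment dates, and that each review covers all logs on file.
   - OA3 falls on days 23–25 (section 6.2.4), which is 22–24 days after visit 2. The chance that a review falls in between is from 22/31 = 0.71 to 24/28 = 0.86.
   - OA4 falls on days 57–61 by section 6.2.4, a gap of 56–60 days. If visit 7 is taken as day 21 (day 24 minus 3), the window of 28 ± 4 days after it gives days 45–53, a gap of 44–52 days. Either gap exceeds 31 days, so at least one review precedes OA4.

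   These fractions describe opportunity for exposure. They say nothing about whether a given PI noticed an arm, assessed that participant or was influenced.

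5. **Later processing.** Reading of data from any time point, OA1 and OA2 included, may follow a review. Exposure here depends on how much judgement the step involves and on whether a PI performs it; the documents do not give the PIs' share.

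**The case against.** The best defence is that 10.3.3 is silent on masking and does not order an unmasked review. Read together with 6.2.3 and 7.2, it could be taken to mean a review of masked or aggregated material, and the plan does not say exactly what the PIs receive each month. That shows the sponsor may have intended something safe. It does not remove the conflict, because masked or pooled material cannot answer a per-participant question and 10.3.3 makes no reference to the limit in 6.2.3.

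Several stronger readings are tempting and go beyond the documents:

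- **That the logs reveal every participant's arm.** They carry no arm label and point mainly to manipulation.
- **That every mechanistic outcome is biased.** OA1 and OA2 are collected before any review. Much of the measurement is also protocolized: fixed pre-load and tap force averaged over 10 reflexes, computed joint angles, pixel-by-pixel T2. Students and staff share the assessments with the PIs.
- **That investigator blinding is the trial's only protection.** Providers are blinded to the hypotheses and kept out of assessment, and there is a sham arm, equal contact time and an expectancy and credibility measure.
- **That the statistician is unblinded.** Section 9.2 says "The study statistician will use the R statistical language to block-randomize treatments stratified by sex", which might suggest it. However, the coordinator makes the assignments, and release of identifying codes only at the end suggests that the arms are coded. Generating a list does not show who received what.
- **That assessors could exploit the checklist line "If necessary repeat a trial and delete prior file".** This is a question of data retention. It does not follow from 10.3.3 and is not part of this point.

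**Conclusion.** The conflict is real and can be verified from the text. Followed literally, 10.3.3 (Metrics) breaks the blinding promised in sections 3, 5.2, 6.2.3 and 9.2 for people who also collect and analyse the physiological outcomes. Its reach is collection at OA3 and OA4, plus later processing that involves judgement, such as T2 regions of interest. Collection at OA1 and OA2 is little affected. So are NPR and RMDQ, which participants report themselves while already aware of their group. The size of any bias cannot be computed, and the documents do not show that bias occurred.

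The conclusion rests on two readings: that treatment administration records means the per-visit Intervention Administration Logs, and that the check is made participant by participant, as its wording indicates. The plan should be changed, and the correction is small.

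**What to change.** Reword 10.3.3 (Metrics) so that it agrees with 6.2.3 and follows the practice in 7.2:

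- The unblinded study coordinator, who does no assessments, carries out the monthly per-participant review of the treatment administration records.
- Clinical questions go to a clinician who does not assess outcomes, such as the medical director.
- The PIs receive only masked or pooled summaries, for example counts of sessions delivered, sessions missed and deviations over all arms, with no thrust, repetition or audible-response entries by participant.

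This is a change of wording that uses existing roles and adds no visits or participants. It has two costs. The PIs lose direct sight of treatment fidelity during the trial. The coordinator, who assigns the arms, would also check delivery, so that check is less independent. An occasional look at a sample of logs by the Independent Monitoring Committee, whose remit in section 12 covers all aspects of the study, could offset the second cost if the sponsor wishes.

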#### **10.3.4 Protocol Deviations**

A checklist of potential protocol deviations will be created and maintained for tracking by the Steering Committee (see appendix). Each protocol violation report will include a description of the violation, the type of deviation that occurred, whether the date the deviation occurred, and whether the IRB was notified. The Steering Committee will review protocol deviations on an as needed basis to determine if subjects should continue in the study, the impact on the procedures, and the next steps for subject continuation. Examples of protocol violations include enrollment of an ineligible subject, randomization of an ineligible subject, failure to collect all screening tests, serious adverse events not reported in a timely fashion, breach of confidentiality, subject lost to follow-up, and visits outside of time window.

#### **10.3.5 Monitoring**

The Steering Committee will be responsible for study monitoring. This committee will review and approve the study protocol prior to initiation of enrollment, will review SAEs and AEs at least twice annually and will be alerted to any interim concerns. Should any SAEs occur, they will be reported within 24 hours to the PIs.

## 11. PARTICIPANT RIGHTS AND CONFIDENTIALITY

### 11.1 Institutional Review Board (IRB) Review

This protocol and the informed consent document and any subsequent modifications will be reviewed and approved by the Ohio University IRB.

### 11.2 Informed Consent Forms

An initial screening will be conducted with all participants to describe the research study and determine their interest. For subjects who are interested in potentially volunteering for the study the study coordinator and/or principal investigators will meet with interested candidates. At this time individuals interested in participating can ask questions about the study. If they wish to be considered for the study they will then be asked to read and sign an informed consent document. A signed consent form will be obtained from each participant. The consent form will describe the purpose of the study, the procedures to be followed, and the risks and benefits of participation. A copy will be given to each participant or legal guardian and this fact will be documented in the participant's record. The principal investigators will work with the Ohio University IRB on an as needed basis to make provisions for special populations. For example, if a non-English speaker expresses interest in the study every attempt will be made to convert the informed consent document into their native language and provide a translator during all assessments.

